***Selection criteria for patients***

Inclusion criteria:

- Patients (male or female) older than 18 years

- Hemodialysis due to chronic end stage renal disease

- Contraindications to the use of LMWH in hemodialysis, planned for at least three consecutive sessions because of:

o high risk of bleeding

• active bleeding, whatever the origin

• recent surgery or puncture body (<15 days)

• curative treatment with unfractionated heparin or anti-vitamin K.

o uremic pericarditis

o disease cholesterol emboli

o thrombocytopenia heparin

- Informed Consent signed

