**4- Experimental plan**

***Choice of the experimental plan and justification***

It is a single-center, randomized, open-type N-of-1 trial (cross-over test series randomized in unique individuals). This is an open study since the techniques cannot be blinded ; however the endpoint chosen is objective (clotting or non-clotting of the dialysis circuit), and not amenable to interpretation. Moreover, the patient is not necessary blinded because this should not influence the response. The choice of N of 1 trial is justified because it is important to choose the best technique according to the patient, and the experimental design can provide an individual response and assess the repeatability of the response by the same technique in the same patient. This experimental design is made possible due to the completion of three dialysis sessions per week chronically ineffective a dialysis session to the next session with a rapid assessment (the same day as the dialysis session) of the test main judgment and fact will be selected patients with contra-indication for LMWH for at least 3 consecutive dialysis sessions without heparin. In addition, this experimental design allows techniques comparison across treatment groups.

The unit of randomization will be patient and will be made according to the following scheme:

- A = discontinuous rinses, B = dilution and C = adsorbed heparin
- The 6 possibles sequences of treatments are:
  - ABC
  - ACB
  - BAC
  - BCA
  - CAB
  - CBA

The patient will be randomized into one of six arms and make sure to have a number of patients included multiple of 6 (see calculation of the number of subjects required). Randomization will be by random blocks of varying size. The order of the types of sessions vary all three triplets for the same patient if the dialysis without heparin must be repeated beyond the first triplets. As a patient may contribute to several sequences, the patient will be considered as a cluster randomization.

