**The procedures evaluated are:**

- Discontinuous rinses : injection of 125 ml of isotonic saline every 30 minutes on the arterial line

- Continuous Flushing (" dilution ") : continuous infusion of isotonic saline at a rate of 250 ml / h on arterial line during the dialysis session

- Adsorbed heparin: rinsing the dialysis membrane before the session with 2 l of isotonic saline containing 10,000 units of unfractionated heparin, no injection or infusion of isotonic saline during the dialysis session

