***Stopping rules***

If three consecutive failures to the same technique, randomization will continue on the remaining 2 techniques if the patient needs to continue its sessions without systemic heparin and if 3 months of inclusion are not met.

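### Heparin thrombocytopenia qualifies a patient for inclusion, every randomised sequence includes the heparin-primed membrane, and the protocol neither exempts these patients nor explains why the technique covers them

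*Protocol*

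**What the plan says.** **Eligibility.** Section 4, Selection criteria for patients, admits patients under the heading "Contraindications to the use of LMWH in hemodialysis, planned for at least three consecutive sessions because of". Four reasons follow: a high bleeding risk (with its own sub-list), uremic pericarditis, cholesterol emboli disease, and "thrombocytopenia heparin". The last stands at the same level as the bleeding-risk item, not inside its sub-list.

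**Allocation.** Section 4, Choice of the experimental plan, codes the techniques as "A = discontinuous rinses, B = dilution and C = adsorbed heparin", lists the six orders of these three, and states "The patient will be randomized into one of six arms". No restricted set of sequences is given for any subgroup.

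**Technique C.** Section 6 defines it as "rinsing the dialysis membrane before the session with 2 l of isotonic saline containing 10,000 units of unfractionated heparin", with no saline injected or infused during the session. Section 6 does not say what happens to the heparin afterwards. That comes from the AN 69 ST item in section 2, which describes the heparin as bound to the membrane and acting locally.

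**Dropping a technique.** The only rule that removes a technique for an individual patient is in section 8, Stopping rules: "If three consecutive failures to the same technique, randomization will continue on the remaining 2 techniques".

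**The concern.** Read together, the eligibility list and the randomisation scheme assign a heparin-primed membrane to a patient whose stated reason for entering the trial is a thrombocytopenia attributed to heparin. The protocol neither exempts this patient nor says why technique C is considered suitable. What is at stake first is safety: a site that follows the document exactly has no instruction for this category.

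There is a secondary statistical point. If the gap were closed informally at the bedside by leaving C out, C would be missing for a reason tied to the patient's condition, and the A-versus-C pairs from that patient would be lost. The protocol does not say how such a patient would be randomised or analysed.

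**Working it through.** No sample size, power or error rate bears on this point, and the plan gives no figure for it to reproduce. The check is a count of sequences and a search for an exemption.

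**Step 1: does any sequence avoid C?** The sequences in section 4 are ABC, ACB, BAC, BCA, CAB and CBA. Each contains C exactly once, so 6 of 6 include it. The order may change in later triplets, but only these six orders are listed.

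**Step 2: how many C sessions does that imply?**
- Per completed triplet: 1.
- Ceiling from section 4, Duration of participation (12 triplets): 12 × 1 = 12 sessions.
- A patient who reaches the individual analysis of section 8 at 18 sessions has completed 18 / 3 = 6 triplets, hence 6 sessions with C.
- About 60% of all patients are expected to need 3 to 6 sessions (section 8, Main Analysis), that is 1 to 2 triplets and 1 to 2 sessions with C. This share is not specific to the heparin thrombocytopenia category.

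**Step 3: is there an exemption anywhere?**

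| Section | What it covers | Does it settle this category? |
|---|---|---|
| 4, Exclusion criteria | Acute renal failure, poor access, transfusion or nutrition during dialysis, severe hypotension, high hemoglobin; the rationale concerns risk factors for circuit clotting | No |
| 5, Study exit | Early termination, end of follow-up, consent, change of center, death, interim superiority | No |
| 8, Stopping rules | A technique is dropped after three consecutive failures | No. It responds to failure of the technique, so C would first have to be used three times |
| 9, Safety | Expected events are those of the underlying condition and those of circuit clotting | No. Heparin exposure under C is not discussed |

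**Step 4: does the stated rationale for C reach this category?** Section 2 introduces the techniques as ways to avoid systemic anticoagulation when bleeding risk is high. The local-action argument for the AN 69 ST membrane answers that problem. Heparin thrombocytopenia is listed in section 4 as a separate reason, outside the bleeding sub-list, and section 3 (Primary objective) describes the population as contra-indicated to heparin, not only to LMWH. Nothing connects the local-action argument to this reason for inclusion.

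**The case against.** The strongest reply is that the sections sit awkwardly together but do not contradict each other on their face.

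- **The criterion concerns LMWH, whereas C uses unfractionated heparin.** The same list admits patients on curative unfractionated heparin, so it is not a list of people who may never meet heparin. This stands as a description of the list. It does not settle the point, because the item in question names heparin itself and the primary objective speaks of heparin generally.
- **C is presented as local, with no anticoagulant added during the session.** This is the sponsor's only stated rationale and belongs among the texts to reconcile. It addresses systemic anticoagulation and is silent on this category.
- **The item is two words of rough translation and is not defined.** This is true, and heparin-related thrombocytopenia is a reading, though the natural one. If something else was meant, the eligibility text needs correcting anyway.
- **Few patients would reach 12 sessions with C.** This is fair: 12 is a ceiling, and the failure rule, the individual analysis or a short contra-indication can end exposure earlier. None of these prevents C from being assigned in the first triplet.

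A reader might go further and infer that the protocol itself declares C contra-indicated in these patients, so that the eligibility list and the six sequences cannot both stand. The document does not say so. That step needs a clinical judgement which the text neither makes nor rules out. A reader might also infer that staff will skip C and bias the comparison, or that only a handful of patients are involved. Nothing in the document supports either inference.

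**Conclusion.** The point holds as an unreconciled safety conflict in the protocol text and has to be fixed. All six sequences assign C, no section exempts patients included for heparin thrombocytopenia, and the only rationale for C does not address them. The size is one heparin-primed session per triplet, with a ceiling of 12 per patient. The number of patients affected is not stated and cannot be derived, so no effect on sample size or on the A-versus-C estimate can be computed.

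The conclusion rests on one assumption: that the two-word item means heparin-related thrombocytopenia. Its weight comes from the safety text alone. The loss of A-versus-C pairs through informal skipping of C is hypothetical and unquantified, and adds nothing to the severity.

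**What to change.** The sponsor, together with those clinically responsible and the ethics committee, should reconcile five places for this category: the AN 69 ST rationale in section 2, the randomisation scheme, the inclusion criteria and the exclusion criteria in section 4, and the definition of C in section 6. The eligibility item should also be worded so that its meaning is clear. Which clinical rule results is for them to decide.

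The statistical text must then follow that decision. If every category is to receive all three techniques, the protocol should state the reasoning for this one. If any category is not assigned all three, its restricted sequences should be written into the randomisation list, and the analysis should treat it as a planned incomplete design and say which comparisons it contributes to. It should not be left to case-by-case omission of a session.

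The cost is a short amendment to the eligibility or randomisation text. Section 10 already gives a changed inclusion criterion as an example of a change to be notified to the ethics committee.

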**Exclusion criteria:**

- Acute renal failure

- Nonfunctional vascular access (blood flow rate below 250 ml /mn)

- Need for perdialytic transfusion of blood products

- Need for perdialytic parenteral nutrition

- Severe arterial hypotension (systolic blood pressure less than 80 mmHg)

- Hemoglobin greater than 13 g/dl

Rationale: risk factors for clotting of the extracorporeal dialysis circuit are the duration of the session, a blood flow of less than 250 ml / min, performing of a blood transfusion or parenteral nutrition during the dialysis session, and hemoglobin > 13 g / dl (Keller, Seemann et al. 1990) (Schultze, Hollmann et al. 1992) (Sepulveda, Davis et al. 1997) (Sperschneider, Deppisch et al. 1997).

***Mode of recruitment***

Monocentric study: patients treated by chronic hemodialysis at the Necker Hospital will be included. Given the number of sessions performed annually at our center (about 7500), the frequency of dialysis prescriptions without systemic anticoagulation (about 10% of cases) representing fifty patients a year to meet the inclusion criteria, we expected inclusion of a period of 18 months would be necessary.

***Expected number of people and justification***

In this study, 78 patients will be included. See the statistical section.

***Duration of participation***

The duration of participation of each subject will be at least 1 week to 3 months maximum (or 12 triplets).

**5- Design and conduct of research**

***Follow-up***

Each dialysis session includes a medical examination and a nurse monitoring. The information session is recorded in the case report form, some data are automatically transmitted by the generator to the dialysis Sined Medware ® software and recorded in the secure medical file of the patient. The estimated dialysability urea by the generator induces no extra cost.

Information contained in the protocol specification

At the beginning of the session

• weight, blood pressure, heart rate

• since the last session : weight gain and symptoms occurred

Monitoring of the dialysis session

• Continuous (Sined Medware ® Software generator Hospal Integra ®: blood flow, venous pressure, ultrafiltration rate, urea dialysance)

• every 30 ': blood pressure, heart rate.

• incidents during the session: clotting of the circuit (partial / full), clinical symptoms.

At the end of the session: session duration, weight, total urea dialysance

***Total duration of the Essay***

Inclusion (24 months months) and follow-up (1 week to 3 months): 27 months maximum

***Study exit***

The inclusion of a patient in the research protocol will end

• in case of premature termination (before three successive sessions are conducted)

• at the end of the maximum period of scheduled follow-up (3 months)

• withdrawal of patient’s consent (at any time)

• in case of permanent change of dialysis center

• in case of death

• in case of a technical superiority in the interim statistical analysis (see page 14)

Patients will be supported by the usual care practices in each dialysis center.

**6- Procedures evaluated**

**For all patients :**

- 3 hemodialysis sessions of 4 hours per week

- vascular access : arteriovenous fistula (mono or biponction with 15 G needles) or dual lumen central catheter

- blood flow : 250 to 300 ml / min

- dialysate : flow 500 ml / min, sodium conductivity 14.4 mS / cm ; bicarbonate conductivity 3.3 mS / cm, temperature 36 °C

- Dialysis membrane : AN 69 ST (NEPHRAL 400 ST)

**The procedures evaluated are:**

- Discontinuous rinses : injection of 125 ml of isotonic saline every 30 minutes on the arterial line

- Continuous Flushing (" dilution ") : continuous infusion of isotonic saline at a rate of 250 ml / h on arterial line during the dialysis session

- Adsorbed heparin: rinsing the dialysis membrane before the session with 2 l of isotonic saline containing 10,000 units of unfractionated heparin, no injection or infusion of isotonic saline during the dialysis session

**7- Endpoints**

***Main criterion***

Need to suspend the session for clotting of the dialysis circuit, because of either :

o complete coagulation of the circuit

o partial coagulation of the circuit (a clot is found in the lines or the bubble trap *)

o increased venous pressure (PV) of the circuit more than 50% beyond its initial value

* Note: the opacity of the fibers of the membrane NEPHRAL 400 ST makes it impossible the assessment of a partial internal filter clotting.

***Secondary endpoints***

1. Loss of dialysis efficiency

- Urea dialysance during the session (online measurement)
- hyperhydratation (weight at the end of the session: + 0,500 kg over the dry weight)

1. Dialysis session tolerance

- clinical secondary effects (headache, cramps, symptomatic arterial hypotension)
- any bleeding in the 48 heures following the dialysis session

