Concerning the analysis of secondary endpoints, the same approach as above will be used for categorical variables. For quantitative variables, we also deem a treatment effect, period and order using a mixed model in which the subject will be returned as a random effect and to take into account the repeated nature of the data.

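### End-of-session overhydration is analysed without starting weight, so fluid left by the previous session's technique understates the contrast between techniques

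*Protocol*

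**What the plan says.** Under Secondary endpoints, loss of dialysis efficiency includes "hyperhydratation (weight at the end of the session: + 0,500 kg over the dry weight". The cut-off refers to dry weight, not to the weight at the start of the session.

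The Experimental plan randomises patients to orders of A (rinses), B (dilution) and C (adsorbed heparin): "The 6 possibles sequences of treatments are" ABC, ACB, BAC, BCA, CAB and CBA. The sessions are consecutive ("contra-indication for LMWH for at least 3 consecutive dialysis sessions without heparin"), at "3 hemodialysis sessions of 4 hours per week", with no washout. For later triplets, "The order of the types of sessions vary all three triplets for the same patient", which can mean a new order at each triplet or at every third. The design is justified by a poorly translated clause, "ineffective a dialysis session to the next session", which appears to say that one session has no lasting effect on the next.

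In the statistics section, categorical secondary endpoints follow the approach of the main criterion, a marginal and a subject-specific model with order or group effects as the named covariates. For quantitative variables, "we also deem a treatment effect, period and order using a mixed model". Neither names starting weight. The Follow-up section does record weight at the beginning of each session, and "since the last session : weight gain and symptoms occurred".

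**The concern.** A clot in one day's circuit says little about the next circuit, but body weight persists. The Justification of research itself accepts that a session shortened by clotting can end above dry weight. That fluid is part of the next session's starting load, and the next session usually uses another technique. A session can then be scored as overhydrated partly because of the technique before it.

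The Summary and the Expected Results state the hope that adsorbed heparin reaches dry weight more often. If part of the excess left by rinses or dilution is counted against adsorbed heparin, that comparison is weakened, and a real advantage could be missed.

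**Working it through.** **The plan's own figure.** The protocol gives no rate, effect size or power for overhydration, so there is nothing to reproduce for this endpoint. The nearest figure is 294 session pairs for clotting, A against B. With success rates of 70% and 80% and independence, the discordant share is 0.30×0.80 + 0.70×0.20 = 0.38 and the ratio is 0.24/0.14 = 1.714. The McNemar formula then gives 296 pairs. A against C gives 65, as stated. This only confirms that the clotting rates used below (30%, 20%, 10%) are the plan's own.

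**Who inherits from whom.** Within a triplet, positions 2 and 3 always follow a different technique. If each triplet gets a new random order, the first session of a later triplet follows the same technique with probability 1/3. If the order is repeated, it never does. Over two to four triplets, 0% to 9% of sessions follow the same technique.

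**Saline load** (Procedures evaluated, 4 h session):
- A: 125 ml every 30 min, 7 or 8 injections, 0.875 to 1.0 L
- B: 250 ml/h × 4 h = 1.0 L
- C: none

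The techniques thus differ in clotting and, for C against A and B, by about 1 L of fluid.

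**Analytic check.** Let excess(t) = technique effect + patient effect + ρ × excess(t−1) + noise. Here ρ is the share of the previous excess still present at the end of the next session. The documents give no ρ, so it is an assumption. With technique effects a, b, c, the mean for A over one balanced triplet, apart from terms common to all techniques, is

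a + (2ρ/3 + ρ²/3) × (b + c)/2.

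Subtracting the same expression for C gives

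A − C = (a − c) × (1 − ρ/3 − ρ²/6).

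| ρ | share of the true contrast seen |
|---|---|
| 0 | 1.00 |
| 0.25 | 0.91 |
| 0.5 | 0.79 |
| 0.75 | 0.66 |
| 1 | 0.50 |

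A period or order term does not change this, because the inherited excess depends on which technique came before. Conditioning on starting weight returns the ratio to 1.00.

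**Binary scale.** With mid-range assumed rates and two triplets, a risk difference of 0.25 becomes 0.23, 0.19, 0.13 and 0.09 at ρ = 0.25, 0.5, 0.75 and 1. If overhydration is rare (3% against 15%) and only positive excess is carried, it stays near 0.12 to 0.13 up to ρ = 0.5 to 0.75.

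**Simulation with a removal limit.** Clotting was 30/20/10%, with clot time uniform over the session. Assumed, because the documents do not give them: interdialytic gain 1.5 to 2.3 kg, +0.7 kg over the long gap, and a removal limit of 3.6 to 6.0 kg per session. Ten settings were run, with and without the saline load. The reference is the within-session A − C effect at the same starting weight.
- Starting excess was higher before C than before A in every setting.
- The unadjusted A − C difference in end weight was below the reference in every setting. Examples at gain 2.3 kg and limit 3.6 kg: 0.21 against 0.27 kg without saline (1 − 0.21/0.27 = 22% too small), and 0.45 against 0.70 kg with saline (1 − 0.45/0.70 = 36% from rounded figures, about 35% unrounded).
- Over all settings the understatement ran from about 3% to 35%. It was smallest where the limit was high and the inherited excess was mostly removed.
- Adjusting for starting excess recovered the reference to within about 4%.

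**The case against.** **Direction.** A reader might infer that carry-over always shrinks A − C compared with a trial that had none. The documents do not support that. With the saline load and a gain of 1.5 kg, the binary difference rises from 16.8 to 17.4 points when carry-over is switched on. Heavier starting loads meet the removal limit more often, so the saline matters more and the within-session effect itself grows. What holds is narrower: the unadjusted contrast lies below the effect at equal starting weight. This also answers the worry that adjustment overstates the benefit of C. It looks too large only beside a trial without carry-over, and it is close to right for the sessions actually run.

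**Position.** It would be wrong to say that C always follows A or B. C comes first in CAB and CBA, two of six sequences, and in a first triplet it then follows a session outside the trial.

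**Size.** No gain, removal limit, overhydration rate or persistence is in the documents. If the next session fully removes the inherited excess there is no bias, though no rule in the protocol ensures this. The objection stands.

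**Premise.** The no-carry-over clause runs on to the same-day assessment of the main criterion, and the later statement that sessions are independent supports the individual Fisher test on clotting. Neither is claimed expressly for weight, so this is an unqualified premise, not a contradiction.

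**Place.** A covariate could be left to the SAP. That is fair in part. But the protocol itself fixes the absolute end-weight definition and names the model terms, so the gap is visible here.

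**Conclusion.** The point holds in limited form. Absolute end weight, consecutive sessions under alternating techniques, and model terms that omit starting weight together make the session-level contrast smaller than the effect at equal starting weight. This matters mainly for adsorbed heparin against rinses and dilution. A and B carry nearly the same saline volume and would differ mainly through sessions cut short by clotting.

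The understatement of A − C, about 3% to 35% on the kg scale, rests on assumed gains and removal limits. It is zero if inherited excess is fully removed, and on the binary scale it can be negligible when overhydration is rare. No single percentage should be quoted as the loss. A reader might also infer that the clotting comparison is affected. Nothing in this argument touches the primary endpoint.

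**What to change.** Keep the +0.5 kg endpoint, and in the paragraph on secondary endpoints:
- Add start-of-session weight minus dry weight as a covariate in the binary model, using the dry weight prescribed before that session.
- Report end weight minus dry weight as a supportive continuous analysis with the same covariate.
- Report each patient's first session as a sensitivity analysis, which is free of carry-over between study techniques. It is a between-patient comparison with only about 78/3 = 26 patients per technique, so it checks direction and has little power.

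In the Experimental plan, limit the statement that one session does not affect the next to the clotting endpoint.

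The cost is wording and one covariate. Start weight is already recorded at every session, before that session's technique acts. The one thing to confirm is that the case report form holds the dry weight in force before each session. No procedure, sample size or primary analysis changes.

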We also hope to demonstrate that the technique of "adsorbed heparin" ( i) better preserves the porosity of the dialysis membranes, maintains throughout the session a satisfactory removal of uremic waste ( Romao , Fadil et al. 1997), (ii) avoids the intake and ultrafiltration liquid rinse or dilution, helps to reach more often at the end of the session the dry weight of the patient and / or are better tolerated clinically (secondary endpoints).

Dilution and adsorbed heparin are used by a small but growing number of nephrologists during hemodialysis sessions without LMWH. The results of the first prospective trial in the field would rigorously validate their effectiveness, and promote their recognition and distribution within the nephrology community. Implementation throughout the course of these two dialysis techniques without systemic heparinization would theoretically have several advantages (our study did not seek to assess), such as reduced transfusion requirements or erythropoietin, or the reduction of nursing work .

In daily practice, the results of this study will be of great use for the whole community : the superiority of the dilution over the rinse could be generalized to all types of dialysis membranes, while the technique of adsorbed heparin would be exploited by the centers using AN69 ST membrane, which cost is quite high.

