**8- Data management and statistics**

***Justification of the number of patients to include***

The calculation of the number of subjects to include derives from the MacNemar test comparing groupes paired for a binary criteria:

|  | Response to treatment B | | | |
| --- | --- | --- | --- | --- |
| Response to the traitement of reference | Failure | Success | Total | Anticipated  Proportion |
| Failure | *r* | *s* | *r+s* | 1 - |
| Success | *t* | *u* | *t+u* |  |
| Total | *r+t* | *s+t* | Npaires |  |
| Anticipated  Proportion | 1 - |  |  |  |

This calculation is based on the estimation that =s/t measures the degree by which a patient will have a success with the reference treatement and a failure with treatment B, compared to failure with the reference treatement and success with treatment B. Of note, patients (*r+u*) having success-success or failure- failure are not taking into account in this calculation. The latter is based on anticipation of marginal probabilities of success, et , defined by the absence of circuit coagulation with each treatement:

- null hypothesis  : 70% in the reference treatment group (30% of clotting), group A,
- = 80% in the dilution group (20% of clotting), groupe B,
- = 90% int the AN 69 ST membrane (10% of clotting), group C,

thus estimating the proportion of discordant pairs :discordant = (*s+t*)/Npairs as well as values

Accoring to published tables, sample size tables for clinical studies, Blackwell Science, 1997 :

- number of pais
- to compare A and B with alpha=5% an a power of at least 80 %, values are for discordant = 0.38 et = 1,7, i.e 294 pairs of dialysis sessions.
- to compare A and C with alpha=5% and a power of 80 %, values are fordiscordant = 0.34 et = 3,85, i.e 65 pairs of dialysis sessions.
- In sum, at least 294 triplets of dialysis sessions are needed, i.e. 882 dialysis sessions, corresponding to 65 patients to recruit over 12 months.
- Each patient being a cluster of dialysis sessions patient, the number of dialysis sessions has to be increased according ta an inflation coefficient based on putative intra-class correlation ( 0.001 to 0.01) ; the inflation coefficient is estimated to range from 1,002 to 1,5 for a mean cluster of 6 dialysis sessions, i.e a raise from 884 sessions to 1323. We finally estimate the need to perform 1050 dialysis sessions in 75 different patients.

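### Fluid removal is defined only as a 0.5 kg cut although end weight is recorded in kg at every session; the kg deviation from dry weight should be analysed beside it

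*Protocol*

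**What the plan says.** Section 7 of the protocol (Secondary endpoints) puts two items under loss of dialysis efficiency: urea dialysance measured online, and "hyperhydratation (weight at the end of the session: + 0,500 kg over the dry weight". The second is the only endpoint on fluid removal, and no reason is given for the 0.5 kg limit.

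Section 5 (Follow-up) records weight at the start of each session and again at its close: "At the end of the session: session duration, weight, total urea dialysance".

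Section 8 (end of Main Analysis) gives two routes for secondary endpoints. In the first, "the same approach as above will be used for categorical variables", meaning the models of the primary endpoint. Quantitative variables are analysed for treatment, period and order effects "using a mixed model in which the subject will be returned as a random effect". The section does not say which route the weight endpoint takes.

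The aim that this endpoint serves is in section 2 (Expected Results and prospects), with a similar statement in the Summary: adsorbed heparin "helps to reach more often at the end of the session the dry weight of the patient".

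**The concern.** The expected mechanism is a matter of volume. By section 6, rinses and dilution each add close to a litre of saline per session, and adsorbed heparin adds none during the session. By section 2, clotting shortens sessions and leaves salt and water removal incomplete. Both effects are graded. Under the cut, a session ending 0.6 kg over dry weight counts the same as one ending 2.5 kg over, and 0.4 kg over counts the same as exactly on target.

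So a measurement already held in kg is reduced to yes or no for one of the named hopes for adsorbed heparin. If ultrafiltration offsets most of the saline and only a modest difference remains, the cut may miss it or estimate it poorly. A null result could then be misread as no fluid benefit.

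**Working it through.** **1. The plan's own figures.** The protocol gives no power, SD, effect or event rate for the weight endpoint. Its only power figures are for clotting: 294 pairs for rinses versus dilution and 65 for rinses versus adsorbed heparin. The paired formula is

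N = [1.96(ψ+1) + 0.8416·√((ψ+1)² − (ψ−1)²π)]² / ((ψ−1)²π).

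- Success rates of 70% and 80%, taken as independent, give π = 0.24 + 0.14 = 0.38, ψ = 0.24/0.14 = 1.714 and N = 296 (stated 294; the rounded ψ of 1.7 gives 305).
- 70% and 90% give π = 0.34, ψ = 3.857 and N = 65, as stated.

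These figures reproduce closely but say nothing about weight. What carries over is the number of sessions: 1050/3 = 350 per technique.

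**2. Volume given (section 6, 4-hour session).** Rinses: 7 or 8 × 125 ml = 875 to 1000 ml. Dilution: 4 × 250 ml = 1000 ml. Adsorbed heparin: none during the session. How much remains at the end depends on ultrafiltration and is not stated.

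**3. Information kept by a cut.** For a normal variable with a share p over the cut, efficiency relative to the mean is φ(z)²/(p(1−p)), where z is the normal quantile of 1−p. Power with the cut is Φ((1.96 + z_power)·√efficiency − 1.96). For example, at p = 50% and 80% kg power: Φ(2.80 × 0.798 − 1.96) = Φ(0.28) = 61%.

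| Share over cut | Efficiency | Cut power if kg has 80% | Cut power if kg has 90% |
|---|---|---|---|
| 50% | 0.64 | 61% | 73% |
| 30% | 0.58 | 57% | 69% |
| 20% | 0.49 | 50% | 62% |
| 10% | 0.34 | 37% | 48% |

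The information lost is 36% at best and 66% when 10% of sessions exceed the cut. The power loss is 17 to 23 points at 30 to 50% over the cut, and 28 to 43 points at 10 to 20%.

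**4. Dependence on the true difference.** This uses 350 sessions per technique, treated as unpaired, two-sided 5%, with the difference in SD units. For kg, power = Φ(d·√(350/2) − 1.96). For the cut, it is the usual two-proportion power.

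| Difference | kg | Cut, 50% over | 30% | 20% | 10% |
|---|---|---|---|---|---|
| 0.10 SD | 26% | 18% | 17% | 15% | 11% |
| 0.20 SD | 75% | 56% | 50% | 43% | 31% |
| 0.30 SD | 98% | 88% | 83% | 75% | 57% |
| 0.40 SD | 100% | 99% | 97% | 93% | 78% |
| 0.50 SD | 100% | 100% | 100% | 99% | 91% |

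At 0.40 SD the loss is 1 to 7 points when 20 to 50% of sessions exceed the cut, but still 22 points when only 10% do. Pairing within patients widens the gap at small differences, because the kg analysis gains more from it. In a paired simulation with 350 pairs, a difference of 0.20 SD, within-patient correlation 0.3 and 30% over the cut, power was 90% in kg and 56% with the cut.

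**5. A skewed case built on the plan's clotting rates.** Clotting is 30% with rinses and 10% with adsorbed heparin, with 350 triplets in 75 patients and a patient-clustered robust test. Assumed, not in the protocol: mean 0.1 kg over dry weight, between-patient SD 0.4 kg, within-patient SD 0.5/0.8/1.0 kg, and clotted sessions falling short by a uniform fraction of 2.5 kg. Clotting alone then shifts the mean by 0.20 × 1.25 = 0.25 kg.

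| Further shift from saline | Cut | kg | Loss (points) |
|---|---|---|---|
| none | 87/71/57% | 99/92/82% | 12 to 25 |
| 0.1 kg | 99/94/85% | 100/100/97% | 1 to 12 |
| 0.2 kg | 100/99/98% | 100/100/100% | 0 to 2 |
| none, heavy-tailed noise (t, 3 df) | 94/84/73% | 99/91/82% | 5 to 9 |

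Repeat runs agree to within a point or two.

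**The case against.** The strongest reply is that the yes/no endpoint fits the question asked. The aim is to reach dry weight more often, which is a frequency, and the share of sessions ending over a tolerance answers it. A mean difference in kg answers a different question. This stands, and it rules out replacing the percentage or reducing it to a descriptive line.

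Second, a signed mean lets sessions ending below dry weight cancel those ending above it, whereas the listed endpoint looks only at excess fluid. This also stands. It is a reason to report both, not to leave the kg measure out.

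Third, section 8 does not assign this endpoint to a model, and a supplementary kg analysis may sit in a statistical analysis plan that is not at hand. That the endpoint will be analysed as binary is therefore an inference. But the definition itself is fixed in the protocol, it is a threshold, and no kg version is listed.

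Fourth, a reader might infer a fixed loss of some 15 to 25 points of power, or that a difference of a few hundred grams will be missed. The documents support neither, because the inputs are not given and the loss runs from almost nothing to more than 40 points. If even 0.1 to 0.2 kg of the litre of saline remained on top of the clotting effect, the cut would detect the difference with 85% power or more in the scenarios above.

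**Conclusion.** The point holds as a missed gain in precision on a secondary endpoint. It is not an error or a contradiction in the protocol. A graded measurement collected at every session enters the endpoint list only as a cut, and under normality that discards at least about 36% of its information.

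The power figures are conditional. The loss is about 17 to 23 points if the kg analysis had 80 to 90% power and 30 to 50% of sessions exceed the cut, and more if fewer do. It is near zero for a true difference of about 0.4 SD or more, provided that roughly 20% or more of sessions exceed the cut. The SD, the residual difference, the within-patient correlation and the share over the cut are all assumptions. Heavy-tailed deviations narrow the advantage of the kg scale. The endpoint is secondary and carries no stated power, so this is a recommended improvement and does not touch the validity of the trial.

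**What to change.** In section 7, keep the percentage of sessions ending more than 0.5 kg over dry weight as a listed secondary endpoint. Add beside it end-of-session weight minus dry weight, in kg.

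In section 8, state that the percentage follows the categorical route. State that the kg deviation is analysed with the mixed model already described (technique, period and order, subject as random effect), with robust standard errors because clotted sessions produce a right tail. Say that the two results are to be read together, since the signed mean lets sessions below dry weight offset those above it.

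The cost is a few lines of text and one more secondary analysis. No patient, session or measurement is added: end weight is already recorded, and the cut already requires dry weight. Because section 5 does not name dry weight among the recorded items, it is worth listing there.
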